# Study protocol of the OrkA project: orofacial and communicative activation in old age– a cluster randomized prevention study in long-term care facilities in Lower Saxony, Germany

**DOI:** 10.1186/s12877-024-04809-5

**Published:** 2024-02-22

**Keywords:** Prevention, Group training, Swallowing, Communication, Cluster-randomized trial, Cognition, Long-term care

## Abstract

**Background:**

The process of aging involves numerous changes in the body, influencing physical, mental, and emotional well-being. Age-related changes and degradation can impact various functions of the swallowing process and lead to delayed word retrieval. Individuals with limited linguistic stimulation may experience a more rapid decline in cognitive performance. Thus, this project explores a preventive training program targeting swallowing and linguistic-communicative skills, aimed at preserving the social participation of older individuals residing in nursing homes.

**Methods:**

A preventive intervention program, combining orofaciopharyngeal and linguistic-communicative components, will be offered twice weekly over 12 weeks in long-term care facilities in the greater Hanover area. The program will aim at: (a) activating sensitive and motor skills in the orofaciopharyngeal area to counter age-related swallowing disorders, and (b) enhancing communicative abilities through semantic-lexical activation. A cluster randomized controlled trial will be conducted to investigate whether the intervention program improves swallowing skills in older adults. Additionally, a secondary analysis will explore the impact on language skills and social participation, as well as program acceptance.

**Discussion:**

The results will provide valuable insight into the effectiveness of preventive measures addressing swallowing and speech issues in older individuals.

**Trial registration:**

The trial was registered with DRKS (German register for clinical trials) in June 2023 (study ID: DRKS00031594) and the WHO International Clinical Trail Registry Platform (secondary register).

**Supplementary Information:**

The online version contains supplementary material available at 10.1186/s12877-024-04809-5.

## Background

Aging is a complex phenomenon influenced by various factors, including genetics, lifestyle, the environment, and health conditions. As individuals age, their bodies undergo numerous changes that affect their physical, mental, and emotional well-being. Understanding the variables associated with the aging process is crucial for the development of strategies to promote “healthy aging” and to prevent age-related diseases.

The ability to swallow sufficiently and safely is not only a primary human need, but also an important aspect of quality of life and participation. Impaired swallowing can lead to malnutrition, as well as aspiration pneumonia. Pneumonia, in turn, ranks among the ten most frequent causes of death in Germany, across all age groups [1]. The act of swallowing comprises oral, pharyngeal, and esophageal phases [2], and age-related changes and degradation impact various functions within these phases. Senescence is often associated with reduced muscle strength, affecting the muscles of the mouth, pharynx, and larynx, as well as the necessary protective reflexes [3]. Dysphagia is diagnosed in 50–60% of all long-term care (LTC) facility residents, and aspiration pneumonia is the fourth most common cause of death in individuals aged 65 and older [4]. These figures underscore the significant need for preventive measures to benefit both aging individuals and the health care system more generally, in terms of cost savings.

Communication is a basic social function that allows individuals to express their needs. Added to this, social interaction is crucial for maintaining psychological well-being. Social interaction and communication both play a role in maintaining cognitive abilities. While it is commonly believed that daily language use results in well-trained linguistic abilities throughout life, it has been observed that, with advanced age, words that are used less frequently are not as easily remembered and require more cues and time for retrieval [4, 5]. Furthermore, studies have shown that cognitive performance declines more rapidly in individuals with limited linguistic stimulation [6]. Declining linguistic abilities are also early indicators of cognitive decline processes, such as those characterizing Alzheimer’s dementia [6].

In recent years, responsibility for the care and support of older individuals has increasingly shifted to LTC facilities [7–9]. Studies have identified correlations between a physically and cognitively inactive lifestyle and age-related decline [10], and the extensive restrictions on contact imposed by COVID-19, especially with LTC facility residents, have increased the likelihood of this detrimental lifestyle condition [11]. Thus, there is a pressing need, particularly within LTC facilities, to establish an activating environment to prevent age-related decline.

This project explores a preventive training program targeting swallowing and linguistic-communicative skills, aimed at preserving the social participation of older individuals in LTC facilities in their everyday lives.

## Methods/design

A preventive intervention program, combining orofaciopharyngeal and linguistic-communicative components, will be implemented in LTC facilities in the greater Hanover area, aimed at prolonging residents’ joint consumption of meals and everyday communication. In more detail, the intervention objectives will be to: (a) activate sensitive and motor skills in the orofaciopharyngeal area to counter age-related swallowing disorders, and (b) stimulate communicative abilities, emphasizing semantic-lexical activation to counter age-related word retrieval disorders.

The cluster-randomized intervention study, utilizing a waiting group design, will aim at testing the following hypotheses:

### Main hypothesis

The orofaciopharyngeal and speech-communication program will help to prevent a decline of swallowing skills in older individuals.

### Secondary hypotheses

The orofaciopharyngeal and linguistic-communicative intervention will:

improve language skills in older individuals;be positively accepted by older individuals within LTC facilities; andimprove the social participation of older individuals, with respect to
everyday communication,swallowing- and eating-related everyday activities, andthe preservation of cognitive abilities.

The project design will follow an MRC phase III approach, based on the Medical Research Council’s (MRC) recommended staged model for complex interventions [12]. A cluster-randomized intervention study with a waiting group design will be conducted, measuring swallowing capacity using the Timed Test of Swallowing Capacity (TTSC) [13] as a primary endpoint. If the intervention proves successful, participants in the control waiting groups will be offered the opportunity to participate after t_2_ (Fig. 1).

**Fig. 1 Fig1:**
[figure not shown]
Schematic overview of the study design

### Characterization of LTC facilities as clusters and participants

The intervention will be implemented in 12 LTC facilities in a group setting, with approximately eight subjects per group. Recruitment will follow a two-stage process. In the first stage, LTC facilities will be recruited. For this purpose, the central supporting organization will contact relevant LTC facilities and members of the research team will introduce the project (i.e., contents, scope of participation, data protection, etc.). Subsequently, interested LTC facilities will be sent detailed project descriptions, to ensure their free, open, and informed participation. The final set of LTC facilities will be determined on the basis of their informed consent of unit managers, number of beds, sponsorship structure (in Germany, facilities are run by profit (i.e., private) or non-profit (e.g., municipal or religious) organizations), and geographical location.

The following inclusion criteria will apply to LTC facilities: (i) located in the greater region of Hanover, (ii) structured by diverse sponsorships, and (iii) providing a regular range of activating group activities (e.g., movement and cognitive training as part of “usual care”). Gerontopsychiatric LTC facilities, facilities for the disabled, and exclusive day care facilities will be excluded. In accordance with cluster randomization recommendations [13], the 12 selected LTC facilities will be stratified by size, sponsorship structure, and resident characteristics, and then randomly distributed to either the intervention or the control waiting group.

In the second step, LTC facility coordinators will recruit 6–10 resident participants from their facility. Prior to this selection, members of the research team will introduce the project within each facility. Participation will be voluntary and will only begin after participants have received detailed information about the study objectives, procedures, and possible consequences, as well as their participant rights. Participants will be able to withdraw their consent at any time. The inclusion criteria for participation will be as follows:

aged 65 years or older and residing in an LTC facility;no mild or moderate frailty (i.e., Clinical Frailty Scale: level < 5), according to Rockwood [14] (as assessed by caring professionals);able to give informed consent (as assessed by caregivers and, if applicable, legal guardians); andsufficiently able to hear (i.e., 80% speech comprehension at an everyday speech volume).

The exclusion criteria will be as follows:

a current diagnosis of a swallowing, speech, and/or language disorder and an associated prescription for speech, swallowing, or language therapy;suspected aspiration (i.e., EAT-10 score > 2);moderate or severe dementia (i.e., DemTect ≤ 8); andestimated life expectancy of < 6 months, based on the “Double Surprise Question” (as assessed by caring professionals) [15].

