### Evaluation

Various evaluation tools will be utilized at three time points (t_0_, t_1_, t_2_) to test the working hypotheses. Assessments of frailty [14, 22] and hearing ability will only be collected at t_0_, to verify the inclusion and exclusion criteria. Table 1 shows the timing of all measurements of individual diagnostic criteria.

**Table 1 Tab1:** Study overview regarding diagnostic measures and time points

time point	study period						
	enrollment	allocation	post-allocation			close-out	
	inclusion of LTC-facilities	statification randomization	pre-inter-vention (t_0_)	intervention	post-inter-vention (t_1_)	6-month follow up (t_2_)	intervention waiting group

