**Enrollment**							
review of inclusion criteria of the LTC-facilities	X						
allocation of the LTC-facilities		X					
informed consent of the LTC-residents			X				

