In addition to the above-described self-assessment tools, some additional questionnaires will be filled in by nursing staff: the Clinical Frailty Scale (CFS) [1, 4], to record patients’ degree of frailty (considering physical, cognitive, and psychological dimensions); and the “Double Surprise Question” [29], to capture life expectancy.

Positive intervention results for swallowing functions and/or communication skills are expected to prompt the implementation and offer of preventive group training programs with respect to swallowing, speech, and language, not only in LTC facilities but also with older individuals, in general.

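### Residents are selected, consented, screened and measured at t0 after their facility has been allocated, with no stated concealment from recruiters, so who enters can differ by arm

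*Protocol article*

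**What the plan says.** Under the heading on LTC facilities as clusters and participants, the article describes recruitment in two stages. The 12 facilities are chosen first and are "stratified by size, sponsorship structure, and resident characteristics, and then randomly distributed to either the intervention or the control waiting group". Residents come next: "In the second step, LTC facility coordinators will recruit" six to ten people each. The research team presents the project on site beforehand: "Prior to this selection, members of the research team will introduce the project within each facility".

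Table 1 gives the same order. The row "allocation of the LTC-facilities" is marked in the allocation column. The row "informed consent of the LTC-residents" is marked at t0, which is the first column of the block headed "post-allocation". The Clinical Frailty Scale, speech audiometry, DemTect, EAT-10 and baseline TTSC carry their first mark in that same t0 column. The description of the study process agrees: facilities are recruited in phase 1, and residents and t0 follow in phase 2.

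Three criteria rest on the judgement of facility personnel: frailty, capacity to consent and life expectancy. The section on assessment tools says of the frailty scale and the life-expectancy question that "some additional questionnaires will be filled in by nursing staff".

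**The concern.** In a cluster trial, randomising facilities makes the facilities comparable in expectation. It does so for participants only if the way they enter cannot depend on the arm. Here a coordinator picks a handful of residents from a whole facility after the allocation has been made. The two arms also make different offers. The intervention arm offers twice-weekly group sessions for 12 weeks. The waiting arm offers three rounds of testing and access to the programme only after t2, if it proves successful. A coordinator who knows the arm may favour motivated or sociable residents for the training groups, and a resident who hears that the facility is waiting may decline.

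If such selection is related to how swallowing capacity changes over the following months, the arms differ for reasons other than the programme. Intention to treat keeps enrolled people in their arm but has no effect on who was enrolled. A larger number of facilities would make the biased estimate more precise without removing the bias.

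**Working it through.** **Order of events, side by side**

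| Step | Recruitment section | Table 1 |
|---|---|---|
| Facility allocation | end of first stage | allocation column |
| Resident selection by coordinators | second stage | not shown separately |
| Resident consent | before participation begins | t0, after allocation |
| Frailty rating, hearing, DemTect, EAT-10 | eligibility criteria | t0, after allocation |
| Baseline TTSC | – | t0, after allocation |

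The text and the table agree, and no other part of the article gives a different order.

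**Safeguards looked for.** The article has different team members do the measuring and the delivering. That concerns outcome assessment and does not mask the people who recruit. The limitations discuss dropout, self-selection of facilities and geography, but not arm-dependent recruitment of residents. The primary test is an unpaired t-test on TTSC change with no covariates named.

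**The plan's own sample size, reproduced.** Inputs from the sample size section: difference 2.8 ml/s, SD 3 ml/s, ICC 0.1, 8 residents per cluster, two-sided 5%, 80% power, 20% dropout.

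- Design effect = 1 + (8 − 1) × 0.1 = 1.7.
- Variance of a cluster mean = 9 × 1.7 / 8 = 1.9125.
- With 5 clusters per arm, SE = √(2 × 1.9125 / 5) = 0.875 ml/s and df = 8. The non-central t gives power of 80.0% (4 per arm gives 66.7%).
- 10 clusters × 8 = 80 residents, and 80 / 0.8 = 100.

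The stated figures hold. Nothing in this point changes the required number.

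**Illustration of sensitivity.** The documents give no figure for the size of a selection effect. The shifts below are assumptions.

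- Take 6 facilities per arm and 8 × 0.8 = 6.4 residents completing per facility, so 6 × 6.4 = 38.4 per arm.
- Design effect = 1 + (6.4 − 1) × 0.1 = 1.54.
- SE = √(2 × 9 × 1.54 / 38.4) = √0.722 = 0.85 ml/s.
- Cluster-level t-test, df = 12 − 2 = 10, no true effect. Rejection probability comes from the non-central t with non-centrality = shift / SE.

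| Assumed shift in mean change | Shift / SE | Type I error |
|---|---|---|
| 0 | 0 | 5.0% |
| 0.5 ml/s | 0.59 | 8.3% |
| 0.75 ml/s | 0.88 | 12.6% |
| 1.0 ml/s | 1.18 | 18.7% |

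A shift of 0.75 ml/s is 0.25 SD (0.75 / 3), or 27% of the target difference (0.75 / 2.8). With the full cluster size of 8, it gives 11.8% (5 per arm, df 8) or 13.6% (6 per arm, df 10), so the result depends little on the dropout assumption.

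**The case against.** The strongest reply is that carrying out an allocation is not the same as disclosing it. The article never says that coordinators know their arm when they recruit, the design figure is not available here, and a fuller protocol might describe concealment. This stands as a limit on wording: the finding is that recruitment can differ by arm, not that it will. It does not remove the point, because the order itself is stated twice and the article describes no concealment from recruiters or residents.

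Other mitigating features are real but partial. The EAT-10, DemTect and hearing criteria are scores or tests rather than staff impressions, which narrows discretion. They do not govern whom a coordinator approaches among eligible residents. The endpoint is a change, so selecting fitter residents biases it only if selection is related to change and not merely to level. Motivation, frailty and expected course could be related to change. The planned comparison of gender, age and frailty would make measured imbalance visible, and baseline adjustment could reduce it. Neither reaches unmeasured selection.

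A reader might go further and infer that the stratification is faulty as well, because it uses resident characteristics before anyone is enrolled and spreads 12 facilities over three factors. The documents do not support this. The phrase can mean each facility's general resident profile, which exists before enrolment. The article gives no levels, crossing or block size from which to calculate imbalance, and it plans 5–6 facilities in each arm.

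**Conclusion.** The concern holds in this form: residents are selected, consented, screened and measured after their facility's allocation, partly on staff judgement, with no stated concealment. Resident selection within facilities is therefore open to the influence of the arm, and the planned primary analysis does not correct for it.

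It would go too far to conclude that randomisation fails to protect the comparison altogether, since facility-level characteristics remain protected. It would also go too far to say that no analysis helps, since adjustment deals with measured differences.

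The 8% to 19% range shows how sensitive the trial is and does not estimate the likely bias. It rests on an assumed shift of 0.5 to 1.0 ml/s, the protocol's SD and ICC, six facilities per arm, 20% dropout and an analysis that already respects clustering. The finding about the order of steps does not depend on those values.

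**What to change.** Change the order in the recruitment section and in Table 1. In each facility, residents are identified, consented, screened and measured at t0 first, and only then is that facility's allocation disclosed to coordinators, caring staff and residents. The t0 column moves ahead of the disclosure of allocation, and the text should say who holds the allocation until then.

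The sample size and the number of visits do not change. The cost is that allocation is announced later. The groups are already staggered because two therapists deliver the programme, so their scheduling takes longer to settle, and the interval from t0 to the first session lengthens somewhat.

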### Ethics

The OrkA project, developed in accordance with the Declaration of Helsinki, was approved by the Ethics Committee of Hannover Medical School, Germany (no. 10650_BO_S_2022) and registered with DRKS (German register of clinical trials) in June 2023 (study ID: DRKS00031594). Any modifications are required to be duly notified and approved in writing.

### Data collection

#### Sample size calculation

The primary outcome variable will be swallowing capacity, as measured via the Timed Test of Swallowing Capacity (TTSC). Based on a two-tailed unpaired t-test with a significance level set to 5% and a power of 80%, *n* = 5 clusters per group will be required (assuming *n* = 8 individuals per cluster). Anticipating a difference in the change in swallowing capacity of 2.8 ml/s between groups, with a pooled standard deviation of 3 ml/s [16] and an ICC of 0.1 [14, 15],^1^*n* = 10 clusters with a combined total of *n* = 80 individuals will be required.

Studies investigating individuals with pre-existing dysphagia in nursing homes [16] and nursing home residents, more generally [17], have reported dropout rates between 10 and 52%. According to the defined inclusion and exclusion criteria, the present study will address less vulnerable residents with no pre-existing dysphagia. Thus, a lower dropout rate of approximately 20% is assumed. On the basis of these assumptions, a sample size of approximately *n* = 100 participants in 10–12 clusters (i.e., 5–6 intervention facilities and 5–6 control waiting facilities) will be required.

#### The OrkA intervention

The preventive intervention will aim at maintaining and improving orofaciopharyngeal and linguistic-communicative competency in older individuals. It will span 12 weeks, with twice weekly 1-hour group sessions. Sessions will be conducted by trained speech and language therapists with experience caring for older patients and expertise in dysphagia and neurology. Each session will comprise two orofaciopharyngeal exercises and two semantic-lexical exercises within a communicative-stimulating environment. Participants may elect to complete voluntary homework assignments based on the contents of each session.

Orofaciopharyngeal exercises will encompass:

orofacial perception (i.e., experiencing the oral cavity and oral stereognosis exercises);tonus and coordination training of oral cavity muscles;isotonic and isometric exercises of facial, lip, and tongue muscles;alternating movements;exercises for pharyngeal and veloparyngeal activation (including airflow control exercises, negative pressure exercises, and laryngeal elevation); andcompensatory aspects, including upright posture, bolus preparation, and postural changes in swallowing techniques.

Semantic-lexical activation exercises will focus on topics relevant to participants’ everyday lives (relating to, e.g., family, seasons, and food), including:

semantic feature analysis (e.g., categorization, sorting tasks, and identification of commonalities);lexical retrieval (e.g., analysis and synthesis tasks concerning word forms);part-whole relations, involving sequences of daily activities; andhyperonyms and hyponyms.

Given age-related decreases in naming accuracy and increases in word retrieval access time [4], these skills will be given special attention through incentivized quick naming (e.g., time competitions, group challenges). Subsequently, appropriately practiced word fields will be integrated into targeted biography-related communication [3, 18, 19].

Based on scientific findings, shared decision making will serve as a guiding principle [20]. Participants will be invited to choose the tasks they practice between sessions and post-intervention [21], with the aim of increasing intervention effectiveness and individual self-efficacy [21]. Studies have shown that rigid exercise frameworks tend to be less accepted and less effective than self-selected aims and content that the individual considers meaningful. Homework completion and success will be documented and discussed at the start of each session. In addition, participants will maintain training diaries, documenting their progress, questions, and problems.

Considering the vulnerability of the participant population, the intervention will be interrupted in the event of acute illness or a crisis-like exacerbation of chronic illness (e.g., apoplexy, aspiration pneumonia). In the event of a deterioration in food intake by more than one point according to the EAT-10, the intervention will be discontinued. An intermediate evaluation of swallowing ability (by means of the EAT-10) will be conducted to continuously ensure patient safety.

